### Recruitment

Patients attending the study pharmacy who are prescribed a salmeterol/fluticasone Diskus® inhaler will be identified via prescription medication records. On attendance to collect their medication in the pharmacy patients will be invited to participate in the study. Interested patients will be screened for eligibility by the pharmacist and if eligible will be provided with information about the study and a copy of the patient information leaflet. Voluntary informed consent will be obtained for all recruited participants.

### Randomisation and allocation

Pharmacies are the unit of randomisation and on enrolment to the study they will be allocated by the lead researcher to one of the three study groups (intervention, comparator or control groups) using a computer-generated (Microsoft Excel® 2013) list of random numbers. In order to control for trial participation effects 10 pharmacies will be randomly allocated to the control group. Remaining pharmacies will then be randomly allocated to either the intervention or comparator group in a 1:1 ratio. Given the nature of the intervention neither pharmacists nor participants can be blinded. All participants are aware that data on adherence are being collected for analysis and a lead-in period is incorporated into the study design to account for a potential Hawthorne effect.

### Pharmacist training

Pharmacists will deliver the intervention allocated to the pharmacy in which they practise and they will receive training specific to that intervention. Training will consist of one 1.5-hour face-to-face workshop with a respiratory physician, nurse specialist and pharmacist educator/researcher where they will be provided with an overview of the study and trained to provide education on inhaler technique and medication adherence. A distance learning study guide specific to each study arm and outlining all study-related procedures will also be completed. Throughout the study pharmacists will be supported by a lead pharmacy researcher who will be available via phone or email to answer any queries they may have.

### Data collection, management and analysis

#### Data collection

Pharmacists completing data collection are trained to understand the importance of robust data collection, are provided with a study guidance pack outlining all relevant data collection procedures and sign a declaration indicating their agreement to keep complete and accurate records. The accuracy, completeness and progress of data will be overseen by a lead researcher in the pharmacy chain where the study is being conducted. This researcher, who will have no role in participant recruitment or in conducting any study-related procedures, will conduct visits to the study pharmacies to check compliance with the protocol.

Every reasonable effort to follow up all enrolled participants for the entire 6-month study period will be employed. At each study visit an appointment for the next visit will be scheduled and non-attenders will be contacted to re-schedule as required. The lead pharmacist researcher will monitor recruitment and retention and target counselling and training interventions to pharmacy sites where retention is a challenge. At any point in time, a study participant is free to withdraw their consent from the study. A patient can be withdrawn from the study by the investigator if necessary, based on clinical assessment of adverse events, or in the event of early discontinuation of the study. In the case of withdrawing from the study, consultation will be completed where possible and their adapted inhaler, peak flow meter and diary will be collected.

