The participants will receive a salmeterol/fluticasone Diskus® inhaler with an INCA® device attached for use twice per day as prescribed. This inhaler will be provided free of charge to all participants, regardless of their health pay status, with the relevant professional service being paid by the patient in the usual manner. For all participants, the INCA® device is used to capture data on adherence and inhaler technique. Participants in the intervention and comparator groups will be asked to record their peak expiratory flow with the eMini-Wright® electronic monitor twice daily. In the intervention and comparator groups participants are also provided with a paper-based diary for recording daily symptoms, medication usage and health care utilisation. This diary, based on the Asthma Society of Ireland’s peak flow diary [21], has been developed specifically for this study and piloted in a sample of seven patients. An extract of the diary is provided in Fig. 2 (see Additional file 1).

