**Fig. 2 Fig2:**
[figure not shown]
Extract of participant respiratory diary

After the initial visit (visit 1), follow-up visits are scheduled 30 (visit 2), 60 (visit 3), 150 (visit 4) and 180 (visit 5) days later. At visits 2, 3 and 5 the participants return their inhalers with the INCA® devices. Visit 4 is a dispensing visit. At each of these visits, for control group participants, changes in medications (including new medications) are recorded as is progress towards the participant’s ‘breathing-related goal’. For intervention and comparator group participants this information is also noted along with the SGRQ responses. Assessment of inhaler technique, using an inhaler technique checklist and inhaler technique training based on assessment observations, is given to both intervention and comparator participants.

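### Adverse-event withdrawal is from the whole study, so later peak flow and diary data from still-consenting participants are lost without need (minor, cheap to fix)

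*Protocol article*

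**What the plan says.** The Data collection section describes two ways out of the trial for an individual. A participant may withdraw consent at any time. Separately, "A patient can be withdrawn from the study by the investigator if necessary, based on clinical assessment of adverse events". One closing procedure follows for anyone who withdraws: a consultation if it can be arranged, after which "their adapted inhaler, peak flow meter and diary will be collected". No intermediate status is described in which the inhaler or recorder stops but follow-up continues. The same section opens its account of retention with the aim that "Every reasonable effort to follow up all enrolled participants for the entire 6-month study period will be employed".

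The measurements concerned are set out under Study design. "Participants in the intervention and comparator groups will be asked to record their peak expiratory flow" twice a day, and in those two groups "participants are also provided with a paper-based diary for recording daily symptoms, medication usage and health care utilisation". After visit 1, "follow-up visits are scheduled 30 (visit 2), 60 (visit 3), 150 (visit 4) and 180 (visit 5) days later". At these visits, "for control group participants, changes in medications (including new medications) are recorded", together with progress on the breathing-related goal. "For intervention and comparator group participants this information is also noted along with the SGRQ responses".

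The secondary outcomes section compares PEFR, SGRQ, rescue medication, diary symptoms and breathing-related goals between the intervention and comparator groups. Statistical methods uses PEFR, rescue medication and symptoms together as the indicator of exacerbations per patient, and plans an intention-to-treat analysis.

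**The concern.** Stopping a treatment or device for safety and leaving the trial are different events, and this paragraph treats them as one. A participant who has an adverse event but is still willing to be followed can be removed, and the two instruments for daily outcome recording are then taken back. Neither the peak flow meter nor the diary needs the acoustic recorder, and nor does the SGRQ, so nothing about stopping the inhaler requires these measurements to stop.

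At stake are the secondary clinical comparisons. Removal for an adverse event can be related to the person's clinical course, which is what PEFR, symptoms and the exacerbation indicator are meant to describe. The missing values therefore need not resemble the observed ones. The Discussion says that the intention-to-treat analysis will take account of loss to follow-up, but no analysis can recover measurements that were never taken.

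**Working it through.** The article states no figure for this point, so there is none to reproduce. The check is first a reading of the text, then a count of what one removal costs.

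**1. Who is covered.** Withdrawal of consent has its own sentence. The investigator route must therefore include people who have not withdrawn consent.

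**2. Which later data stop, by source.**
- PEFR: needs the peak flow meter, which is collected. It cannot continue.
- Diary symptoms: need the diary, which is collected. They cannot continue. Entries already made are secured.
- SGRQ and breathing-related goal: recorded at study visits. The article does not say that visits end, but it provides none for a person withdrawn from the study. Probably lost.
- Rescue inhaler, steroid and antibiotic dispensing: Study design takes the baseline history of these from the pharmacy medication record, and the secondary outcomes section reviews dispensing records before, during and after the study (there for adherence). Nothing says that access ends at withdrawal. May be recoverable.
- Device-measured adherence (primary): needs the Diskus with its recorder. If that inhaler is stopped, the data end whatever the wording.

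**3. Loss per removed participant, intervention or comparator group.** Inputs are the visit days (30, 60, 150, 180) and twice-daily PEFR, both from Study design.
- Days lost = 180 − removal day: 150, 120 or 30.
- Share of 180 diary days: 150/180 = 83%, 120/180 = 67%, 30/180 = 17%.
- PEFR readings lost = 2 × days lost: 300, 240 or 60.
- SGRQ visits remaining after visit 2, 3 or 4: at most 3, 2 or 1 (visit 4 is mainly for dispensing).

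**4. Effect on an arm comparison, as an illustration only.** The number removed and their exacerbation rate are not in the article. Assume 1 of 75 removed, in one arm only, with twice the exacerbation rate of the others, and no recovery of their later events from records.
- Full follow-up, in event units: 74 × 180 + 2 × 180 = 13,680. Person-days: 75 × 180 = 13,500.
- Events lost: 2 × 150 = 300 (2.2%), 2 × 120 = 240 (1.8%) or 2 × 30 = 60 (0.4%).
- Factor on the between-arm ratio, per patient: 13,380/13,680 = 0.978; 13,440/13,680 = 0.982; 13,620/13,680 = 0.996.
- Factor per person-time: (13,380/13,350)/(13,680/13,500) = 0.989; (13,440/13,380)/(13,680/13,500) = 0.991; (13,620/13,470)/(13,680/13,500) = 0.998.
- One such removal in each arm at the same time and with the same rate ratio: the factors cancel, giving 1.00.

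More removals confined to one arm would enlarge these departures. The article gives no basis for choosing the number, so this is not an estimate.

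**The case against.** The clause is short and conventional, and it sits in a condensed article. It is limited to necessity and clinical assessment. The article mentions a guidance pack for data collection and arm-specific study guides, neither of which is shown, and these might provide for follow-up after withdrawal. This stands for the SGRQ and goal visits, whose end is inferred. It does not stand for the meter and diary, because the article itself states that they are taken back.

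A reader might call the clause a contradiction of the six-month follow-up aim. That goes too far: a promise of reasonable effort allows a discretionary clinical exception. The two are in tension, and no more.

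A reader might also infer that every non-device outcome is lost, or that all three arms' comparisons suffer. The documents do not support this. Rescue dispensing may remain available from pharmacy records. Health care use is written in the diary but is not a named outcome. The control group has no diary and no follow-up SGRQ, and the secondary clinical comparisons are between the other two groups.

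Finally, the effect is likely to be slight. All arms use the same drug, and Safety reporting says that the recorder does not interfere with its delivery. Removals should be few, and no reason is given for them to differ by arm. This stands, with one reservation: pharmacists are not blinded and removal is discretionary, so balance is plausible but not guaranteed.

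**Conclusion.** The point holds as a minor improvement. The article fixes a rule under which a still-consenting participant can be removed from the study for an adverse event, and the exit procedure makes later PEFR and diary symptoms impossible to collect in the intervention and comparator groups. Loss of later SGRQ and goal data is probable but rests on inference.

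For the person removed, the loss ranges from 17% to 83% of diary days, depending on the visit at which removal occurs. For the trial, the loss cannot be sized because no removal rate is given. It is probably small, and close to nil if removals are balanced between arms. The factors of 0.978 to 0.998 rest on an assumed single one-sided removal with an assumed rate ratio of 2, and should be read only as showing the order of magnitude in that case.

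A reader might infer that the primary result or the intention-to-treat analysis is compromised. The documents do not support that: the primary endpoint needs the inhaler and recorder in any case, and the concern is limited to secondary outcomes.

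**What to change.** Reword the withdrawal paragraph under Data collection so that an adverse event may lead to stopping the study inhaler or device, at clinical discretion, while the participant stays in follow-up to day 180 unless consent is withdrawn. Participants in the intervention and comparator groups keep the peak flow meter and diary where willing and continue the scheduled SGRQ. The goal and dispensing-record follow-up already planned for a participant's arm continues. Keep the present exit procedure, including return of equipment, for withdrawal of consent.

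The change needs one amended paragraph, which can go through the ethics committee route that the article already describes. Sample size, endpoints and analysis stay as they are. The cost is a few extra contacts, at existing visits or by telephone, and some burden on people who have had an adverse event. Some will decline, so the data will be more complete but not fully so.

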### Safety reporting

Safety testing and a comprehensive risk assessment have been conducted in an effort to minimise potential hazards associated with the clinical investigation of this device. The INCA® device will be securely fixed to the outer casing of the inhaler. It does not interfere in any way with the inhaler’s mechanism of drug delivery. However, in the event of any safety issues arising adverse events and serious adverse events will be recorded in the case report form and evaluated by the lead pharmacy investigator. The principle investigator, ethics committees and the Health Products Regulatory Authority (HPRA) will be notified of any serious adverse events that occur. In addition, information about device-related adverse events will be collected and reported to the manufacturer of the device and the HPRA. Drug-related serious adverse events will be reported to the manufacturer of the drug.

### Data management

Paper-based case report forms will be pseudonymised with a unique patient identifier code. On study completion or withdrawal, data from these report forms will be input by the lead researcher into an electronic, password-protected database. Participant files will remain locked in a secure and accessible place, in a manner consistent with local data protection requirements, and maintained in storage for a period of 3 years post termination of the study.

Audio data will be uploaded to a secure server, access to which is by individual user name and password. Individual pharmacists will not have access to this database. The tool has an inbuilt audit trail that records, and can display, details of additions or changes made to data either on a by-user or a by-patient basis.

### Analysis of the audio data

The INCA® device is a Conformité Européene (CE)-marked device which is manufactured by Vitalograph, Ennis, Ireland. Digital recordings from the INCA® device are analysed as previously described [19]. The files are uploaded to a secure server and analysed using signal processing methods. The sensitivity and specificity details of the signal processing algorithm have been published [24]. The algorithm identifies each audio file as one representing either correct or incorrect inhaler use as well as automatically classifying any technique errors identified. Two independent human raters also over-read all files from all participants in order to validate the data. Comparison is made between the automated and human classification as well as between the classifications of the two independent raters. In the event of any disagreement, review by a third over-reader yields the final classification by majority decision. The final classification is then used in the calculation of the actual adherence. The human raters are independent of any patient care during the trial and are blinded to the randomisation status of the patient. Critical inhaler errors which can occur include failure to prime the inhaler with drug, exhalation into or near the mouthpiece after priming but before inhalation, failure to achieve an adequate flow rate and the presence of multiple inhalations indicating inadequate breath-holds. Non-critical errors such as not holding the device level are not recorded.

### Statistical methods

Statistical analysis will be conducted using IBM SPSS Statistics for Windows, Version 21.0. (Armonk, NY, USA: IBM Corp). Descriptive statistics will be used to evaluate differences in demographic characteristics, clinical condition, medication profile, exacerbation history and quality of life scores between study groups. Categorical variables will be expressed as frequencies or percentages and quantitative variables as means and standard deviations or medians and interquartile ranges.

The primary analysis will be carried out using multilevel modelling (such as mixed linear effects modelling) with the individual as the unit of analysis and controlling for the effects of clustering and baseline differences. An intention-to-treat analysis will be conducted. A secondary, per-protocol analysis will also be conducted. This form of analysis includes only those participants who completed the treatment protocol originally allocated, providing results on the efficacy of the trial.

The proportion of patients achieving good actual adherence (≥80 %) and the proportion progressing to good technique (≥80 % of all doses attempted by the patient classified as correct technique) will be analysed using a random-effects logistic regression with the individual as the unit of analysis and the pharmacy included as the random effect, to control for the effects of clustering.

Changes in patterns of adherence will also be investigated. PEFR, rescue medication use and reported symptoms will be described and used as an indicator of the number of exacerbations per patient which will, in turn, be compared between the groups. Additionally, differences in the SGRQ responses will be examined. For all analyses stratification of patients by diagnosis will be attempted but consideration will be given to the ability to make inferences based on patient numbers.

A full statistical analysis plan will be written by an independent statistical team prior to any analysis being undertaken. Data will be reported in line with the Consolidated Standards of Reporting Trials (CONSORT) 2010 Statement [25] as well as its extension to cluster randomised trials [26] and non-pharmacological treatment [27].

## Discussion

The aim of this study is to evaluate the extent to which a community pharmacist-delivered intervention combining monitored adherence with repeated personalised education can improve inhaler technique and adherence in patients with respiratory disease. This is the first community pharmacy-based study to use a technology that objectively assesses appropriate use of inhalers both in terms of technique of use as well as time of use, permitting longitudinal evaluation of patients’ habitual performance when not under direct visual observation. This technology incorporates a novel electronic device, automated algorithms and feedback tools including graphical representations of adherence, facilitating personalised feedback provided by the pharmacist.

Pharmacists are increasingly involved in comprehensive medication management [28]. In order to optimise clinical outcomes for their shared patients close collaboration between pharmacists and physicians is likely to be required [29]. Provision of high-quality clinical recommendations that improve patient outcomes is important in establishing trust [30], a key component of successful pharmacist/physician collaboration [29, 31]. Collecting objective longitudinal information on inhaler adherence may support the formulation by the pharmacist of such recommendations, thus supporting the collaborative clinical decision-making process. It is expected that some participants may become fully adherent, with others continuing to demonstrate variable or poor adherence over the study period. Combining this information with clinical measures such as PEFR data and exacerbation rates may support inter-professional decision-making for individual patients by potentially distinguishing between patients who would benefit from further interventions to promote adherence as opposed to those in whom therapy adjustment or change of inhaler device may be more appropriate.

As INCA records comprise a much richer dataset than other adherence measures that are routinely available for patients in primary care (primarily prescription refill and dose counter information), analysis of the nature, prevalence and persistence of timing and technique errors identified by the INCA® device should also lead to a deeper understanding of adherence and the barriers to effective Diskus® use, potentially facilitating development of proactive countermeasures for all patients. Analysis of the study data will also provide a means of assessing the reliability of conventional adherence measures in identifying and assessing adherence.

The study has a number of limitations. Patients with asthma and/or COPD are eligible to join the study meaning that there is a lack of sample homogeneity with respect to clinical condition. Stratification by condition at point of analysis will be attempted, but such analysis may lack sufficient power to make valuable inferences meaning that the study may be limited in its generalisability.

Patients requiring regular medication for the treatment of a chronic condition, such as asthma or COPD, are not required to register with an individual pharmacy in the Republic of Ireland meaning that they are free to move between pharmacies when collecting their monthly medication. To avoid the situation where patients collecting a prescription for a salmeterol/fluticasone Diskus® inhaler in a study pharmacy as a one-off occurrence are recruited to the study (leading to greater potential for attrition) the inclusion criteria specify that the patient must have had at least three prescriptions for any medication filled in the study pharmacy in the prior 6 months. Whilst the three prescriptions do not need to have been for a salmeterol/fluticasone Diskus® inhaler this nevertheless raises the possibility that patients with adherence rates of at least 0.5 at baseline will be recruited. However, given that adherence rates based on prescription records frequently overestimate adherence [32], and as the INCA device is designed to assess actual adherence (defined as the number of doses taken correctly at the correct time), we feel that this is justified.

As with other cluster randomised trials where allocation concealment is not possible there is a risk of selection bias [33, 34] both from the pharmacist and participant perspective. To minimise such bias pharmacists in each individual site are trained to recognise the importance of unbiased recruitment and recruitment to each site is monitored by the lead pharmacist researcher so that potential bias can be identified and addressed through further counselling and/or training as required.

There is a potential for loss to follow-up. To minimise these losses, participants not attending for study visits at scheduled times will be contacted by telephone a maximum of three times. Potential loss to follow-up has been accounted for in the sample size estimation and will be taken account of in the intention-to-treat analysis of study data.

